### Statistical analysis of routine data

Statistical analyses will examine whether the intervention (implementation of self-consent) is associated with an increase uptake overall and whether it has the potential to reduce health inequalities.

Routine PHE surveillance reports HPV uptake by geographical area but does not provide data on uptake by other factors such as ethnic group, social position or type of school. We will examine HPV uptake by these factors by extracting information from the Child Health Information System (CHIS).^17^ Following on from our previous work,^5^ we will examine data in relation to the programme years 2014/2015 until the 2018/2019 to compare uptake since the two-dose HPV vaccination programme has been implemented. The data will be anonymised and transferred in an encrypted format from the host organisation to the University of Bristol where it will be securely stored according to the Data Protection (Amendment) Act 2003 and University of Bristol requirements.

The following variables will be available from PHE through extracting anonymous aggregate information from routine immunisation systems and CHIS: number of young people offered HPV vaccination; HPV uptake by source (school, primary care, other); consent (parental written, parental verbal, young women’s self-consent); ethnic group; index of multiple deprivation^18^; childhood vaccinations; school year; year of birth; school; local government area. These data can then be used in analyses of HPV uptake. Measures of effect will be expressed as ORs and risk differences (ie, percentage of HPV uptake before intervention minus percentage of HPV uptake during intervention).

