We will test whether there has been an increase in the uptake of the HPV vaccination programme before and after the intervention in terms of risk difference (difference in two proportions and tests of null hypothesis that there has been no change in uptake). Initiation of HPV vaccination uptake is 84.5% in Bristol and 86.4% in South Gloucester. Each year, approximately 1900 and 1300 (overall 3200) are invited to participate.^19^ Therefore, there will be an 80% power to detect an increase in HPV vaccine uptake to the average in England (89.4%) and over 90% power to detect an increase to 95%. In addition, we will examine whether uptake among young people from less affluent areas, minority ethnic groups and in alternative educational settings has increased and whether there has been any unintended increase or reduction in health inequalities in relation to HPV uptake. We also will examine uptake for specific schools exposed to the intervention and assess whether there is an association between the intensity of implementation of self-consent procedures (as examined in the process evaluation) and HPV vaccine uptake.

The observational data will test whether there has been an increase in HPV vaccination uptake in two ways. First, is there an increase before and after the change in our intervention sites? Second, is there evidence that the percentage change in our intervention sites is different from other sites in England where no such intervention took place? In the second set of analyses, we will seek to select comparison sites that are similar to our intervention sites in terms of ethnic diversity and social position.

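### The stated 80% power to detect a rise to 89.4% does not follow from the plan's own inputs; for the two authorities pooled, those inputs give about 99.9%

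*Protocol article*

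**What the plan says.** All of this is in the protocol article, under Statistical analysis of routine data.

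- **Hypothesis and test.** "We will test whether there has been an increase in the uptake of the HPV vaccination programme before and after the intervention". The method is given as "difference in two proportions and tests of null hypothesis that there has been no change in uptake".
- **Baselines.** "Initiation of HPV vaccination uptake is 84.5% in Bristol and 86.4% in South Gloucester".
- **Numbers.** "Each year, approximately 1900 and 1300 (overall 3200) are invited to participate".
- **Conclusion.** "Therefore, there will be an 80% power to detect an increase in HPV vaccine uptake to the average in England (89.4" per cent), and "over 90% power to detect an increase to 95" per cent.
- **Years of data.** The same section says the data will cover "programme years 2014/2015 until the 2018/2019", which is five programme years. It does not say how they divide into before and after.

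One power figure is given for two authorities that differ in baseline and size. The text does not say whether it is for the two together or for each one.

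**The concern.** The 80% is presented as the consequence of the baselines, numbers and test set out just before it, so it can be checked from the article alone. It should come out of a two-proportion calculation on those inputs, and it does not.

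This is the article's only quantitative justification for the before/after test. Read as a pooled figure, it suggests that a rise of about 4.1 points (85.3% to 89.4%) is near the limit of what the data can detect, when the stated inputs can detect a much smaller one. Read as a figure for each authority, it hides how far the two differ, and how much the South Gloucestershire figure depends on the number of years compared. A reader who later weighs a null or a small effect cannot tell which comparison the 80% was meant to cover.

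**Working it through.** **Inputs from the article.** Baselines 0.845 (Bristol) and 0.864 (South Gloucestershire); annual numbers 1900 and 1300; targets 0.894 and 0.95.

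**Assumptions, not stated in the article.** Two-sided alpha 0.05; independent girls; first, one programme year before against one after.

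**Pooled baseline.** (0.845 × 1900 + 0.864 × 1300) / 3200 = (1605.5 + 1123.2) / 3200 = 0.8527.

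**Formula.** With d = p2 − p1 and p̄ the overall proportion,

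- SE0 = √[p̄(1 − p̄)(1/n1 + 1/n2)]
- SE1 = √[p1(1 − p1)/n1 + p2(1 − p2)/n2]
- Power = Φ[(d − 1.96 × SE0) / SE1]

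**Attempt to reproduce the 80% (rise to 89.4%, one year per period).**

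| Comparison | n per period | d | SE0 | SE1 | (d − 1.96 × SE0)/SE1 | Power |
|---|---|---|---|---|---|---|
| Pooled | 3200 | 0.0413 | 0.00831 | 0.00830 | 3.01 | 99.9% |
| Bristol | 1900 | 0.0490 | 0.01093 | 0.01090 | 2.53 | 99.4% |
| South Gloucestershire | 1300 | 0.0300 | 0.01279 | 0.01278 | 0.39 | 65.0% |

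None of the three is 80%. The number per period needed for 80% power is 1018 pooled, 741 in Bristol and 1854 in South Gloucestershire.

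**Other conventions (pooled, Bristol, South Gloucestershire).**

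- One-sided 5%: 99.96%, 99.8%, 75.8%.
- Two-sided with continuity correction: 99.9%, 99.4%, 62.8%.
- Arcsine: 99.9%, 99.5%, 65.2%.
- Annual numbers halved per period: 94.0%, 88.8%, 38.1%.
- Difference-in-differences against an equal-sized comparison area: 92.5%, 86.4%, 36.6%.
- Pooled only, two-sided alpha 0.01 and 0.001: 99.2% and 95.3%.

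**All five programme years,** two-sided 5%, taking the quoted baseline to hold in every before-year:

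| Before : after years | Pooled | Bristol | South Gloucestershire |
|---|---|---|---|
| 4 : 1 | ≥ 99.9% | ≥ 99.9% | 83.6% |
| 3 : 2 | ≥ 99.9% | ≥ 99.9% | 95.3% |
| 2 : 3 | ≥ 99.9% | ≥ 99.9% | 95.3% |
| 1 : 4 | ≥ 99.9% | ≥ 99.9% | 85.1% |

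With only three years in all, South Gloucestershire has 76.7% (2 : 1) or 78.0% (1 : 2).

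**What does land near 80%.** The constructions found all use inputs that the article does not state:

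- South Gloucestershire with three years before and one after (81.2%), which leaves out one of the five years.
- South Gloucestershire's baseline with Bristol's 1900 girls (81.0%).
- Half of Bristol's annual number with one-sided alpha 0.01 (80.1%).
- Some allowance for clustering by school.

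The article does not say that any of these was used.

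**Rise to 95%.** The term (d − 1.96 × SE0)/SE1 is 11.2 pooled, 8.8 in Bristol and 5.7 in South Gloucestershire, so power exceeds 99.9% in all three. The article's claim of more than 90% is true but very loose.

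**Pooled detectable difference.** With 3200 per period, 80% power is reached at about 87.7%, a rise of about 2.4 points.

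**The case against.** The best defence has three parts.

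*The figure is safe for the main comparison.* The article speaks of overall uptake and of change in the intervention sites jointly, so the pooled comparison is the natural main one. There 80% errs on the low side. The cohort sizes are fixed by who is offered vaccination, so the figure sets no recruitment target. This stands, and it lowers the severity. It does not make the figure right: the sentence draws 80% from inputs that give 99.9%.

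*South Gloucestershire is not shown to be underpowered.* A reader might infer from the 65% that the study lacks power there, and that a null result would be misread. The documents do not support that as a flat statement. The 65% rests on one year per period, whereas the article plans five programme years, and every split of all five gives at least 83.6%. The numbers quoted are annual rates, not sample sizes per period, and no separate South Gloucestershire test is named. This objection stands in full.

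*An article may leave details out.* Alpha, sidedness and any clustering allowance are commonly left to the fuller document, so their absence alone is no finding. That also stands. The finding is that the stated figure does not follow from the stated inputs under any of the usual conventions tried. A reader might also infer a hidden design effect, since one can always be solved for that brings the pooled test down to 80%. The article gives no intraclass correlation and no design effect, so that remains conjecture.

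**Conclusion.** The 80% power for a rise to 89.4% is wrong as written. Severity is minor to moderate.

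For the pooled comparison, the stated inputs give nominal power of about 99.9% with one year per period, and no less with all five years. The stated figure is therefore about 20 points too low. Bristol alone is similar (99.4% or more). For South Gloucestershire alone, the direction depends on the data used: 80% overstates power when about one year per period is compared (65%), and understates it when all five years are used (83.6% to 95.3%).

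These values assume a two-sided 5% test and independent girls. With one year per period, changing to a one-sided test, a continuity correction or the arcsine method does not bring any of the three comparisons to 80%. Correlation within schools would lower every figure by an amount the article gives no means to calculate. The result therefore does not show that the study is underpowered, nor that real power after clustering is as high as 99.9%.

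**What to change.** Replace the power sentence with recomputed power for each comparison the authors intend to make, the pooled one first. State alpha, sidedness, the number of programme years before and after, and that girls are treated as independent.

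On a two-sided 5% test with one year per period, the pooled entry would read: 85.3% to 89.4%, 3200 per period, power 99.9%, detectable rise about 2.4 points at 80% power. If authority-level figures are given, compute them for the split of years actually planned; 65% for South Gloucestershire should appear only if one year per period is the plan.

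If a clustering allowance produced the 80%, state the design effect actually used and its source, and apply it to every figure. Do not insert a design effect or intraclass correlation solved backwards to reach 80%.

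The cost is a few lines of text and a short recalculation. Design, data and analysis do not change.

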In her doctoral thesis, Batista-Ferrer^16^ examined consent for the HPV vaccine in schools in Bristol, UK. Reasons recorded for why eligible girls did not receive the first dose of the HPV vaccine course revealed that lack of a signed parental consent form was the main reason (45.9%), while active refusal by parents occurred much less frequently (11.9%). Nevertheless, research indicates that immunisation nurses and school staff were unwilling to be held accountable if young women presented for HPV vaccination without parental consent.^7 16^

PHE data for 2014/2015 show some areas in the south-west of England with low uptake of HPV vaccination. For example, Bristol was ranked 112th of 119 English local authorities (LAs) (excluding London) and South Gloucestershire was 106th. Because of concerns about low uptake rates, staff at PHE (South West) developed a ‘South West Template Pathway on Self Consent for School Aged Immunisations’. The aim is to support provider organisations in implementing a self-consent process to support young people to easily access vaccines, support immunisers to feel confident about self-consent and to improve the uptake of immunisations.

The current research will focus on the practicality and acceptability of implementing the new self-consent procedures, and the potential impact on overall uptake and health inequalities. This will involve a systematic review of evidence relating to consent procedures for adolescent vaccinations, a process evaluation examining new self-consent procedures in two LAs in the south-west of England and an assessment of the impact of self-consent on overall uptake levels and in relation to SES, ethnicity and type of school.

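### Two tests of increased uptake stand side by side, and nothing says that the controlled comparison, not the uncontrolled before/after test, is the one that supports a claim of impact

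*Protocol article*

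**What the plan says.** The section on statistical analysis of routine data announces the plan: "The observational data will test whether there has been an increase in HPV vaccination uptake in two ways". The two questions are then given in order:

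- "First, is there an increase before and after the change in our intervention sites"
- "is there evidence that the percentage change in our intervention sites is different from other sites in England where no such intervention took place"

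The abstract repeats them as (a) and (b). Neither place ranks them.

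More is fixed for the first question than for the second. The risk difference, one of the measures of effect, is defined as uptake before minus uptake during the intervention. The test is a "difference in two proportions and tests of null hypothesis that there has been no change in uptake", with no trend term mentioned. The power statement follows directly and concerns this contrast. No power is given for the comparison with other sites.

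On how the sites came to be studied, the introduction reports for 2014/2015 that "Bristol was ranked 112th of 119 English local authorities (LAs) (excluding London) and South Gloucestershire was 106th". It continues: "Because of concerns about low uptake rates, staff at PHE (South West) developed" the self-consent pathway. That year lies inside the analysis window: "we will examine data in relation to the programme years 2014/2015 until the 2018/2019".

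On comparators, the methods text says "we will seek to select comparison sites that are similar to our intervention sites in terms of ethnic diversity and social position". The abstract adds a third criterion, initial HPV uptake.

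The strengths and limitations box grants that the study is not a trial, and then says that the routine-data analyses will give evidence of the impact of self-consent on uptake.

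**The concern.** A before/after contrast in the intervention sites alone cannot separate the effect of self-consent from whatever else moved uptake over the same years. Two features make this more than a formality. The sites were near the bottom of the national ranking and were acted on because of it, so some recovery might have come anyway. The data window is also tied to the two-dose programme, and the article does not show that uptake under that schedule was otherwise stable.

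The plan does not say what follows if the two tests disagree. Suppose uptake rises significantly in Bristol and South Gloucestershire, and rises as much in the comparison sites. Followed as written, the plan gives a positive answer to its first question and a negative one to its second. Either could then be put forward as the finding on impact.

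**Working it through.** **Inputs from the article.** Uptake of 84.5% in Bristol and 86.4% in South Gloucestershire; about 1900 and 1300 girls invited per year, 3200 in all; England average 89.4%.

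**Assumptions.** Two-sided 5% level (not stated); one year before against one year after, except where noted; binomial variance only.

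**Pooled baseline.** (1900 × 0.845 + 1300 × 0.864) / 3200 = 2728.7 / 3200 = 0.8527.

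**Formula.** With p1 before, p2 after, d = p2 − p1, p̄ = (p1 + p2)/2 and n per period:

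- SE0 = √[2p̄(1 − p̄)/n]
- SE1 = √[(p1(1 − p1) + p2(1 − p2))/n]
- P(significant increase) = Φ[(d − 1.96·SE0)/SE1]

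**The plan's own figure.** For a rise to 89.4% this gives 99.9% with both authorities pooled, 99.4% for Bristol alone and 65.0% for South Gloucestershire alone. The stated 80% is not reproduced. That is a separate matter, and nothing below depends on it.

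**Before/after test when self-consent has no effect.** Set d equal to an assumed background rise, with n = 3200:

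| Rise | SE0 | SE1 | (d − 1.96·SE0)/SE1 | P(significant increase) |
|---|---|---|---|---|
| 1 point | 0.00873 | 0.00873 | −0.81 | 21% |
| 2 points | 0.00860 | 0.00860 | 0.36 | 64% |
| 3 points | 0.00847 | 0.00846 | 1.58 | 94% |

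With no rise the figure is 2.5%. With two years in each period (n = 6400), rises of 1 and 2 points give 37% and 91%. More data make this worse, because the bias does not shrink as the standard error does. For scale, the rise that the study is planned around is 89.4 − 85.3 = 4.1 points.

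**Regression to the mean.** Binomial error in one year's uptake is √(0.845 × 0.155/1900) = 0.8 points for Bristol and √(0.864 × 0.136/1300) = 0.95 points for South Gloucestershire. The shortfalls from 89.4% are 4.9 and 3.0 points. Sampling noise in a single year therefore explains little of the gap. Anything more would need year-to-year variation within authorities, which the article does not report.

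**Controlled contrast.** A drift shared by both groups cancels. Take a comparator m times as large that stays at 85.27%, and a rise to 89.4% in the intervention sites:

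- SE = √[(0.1256 + 0.0948)/3200 + 2 × 0.1256/(3200m)]
- m = 1: SE = 0.0121; power = Φ(0.0413/0.0121 − 1.96) ≈ 93%
- m = 2: SE = 0.0104; power ≈ 98%

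The uncontrolled difference has SE = √[(0.1256 + 0.0948)/3200] = 0.0083. With m = 1 the controlled standard error is thus about 1.5 times as large (0.0121/0.0083).

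**The case against.** The strongest reply is that the control is already there. Comparing the change with sites that had no intervention is a difference-in-differences question, and it removes a shared trend. The abstract's matching on initial uptake would also reduce regression to the mean in that comparison. This stands: a reader might infer that the study has no control, and the article does not support that.

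Second, the before/after null is that uptake has not changed. If uptake really rises for background reasons, rejecting that null is correct. This also stands, so the 21%, 64% and 94% are not error rates of the test as worded. They are the chance of a wrong conclusion if the result is read as an effect of self-consent. The article leaves that reading open: it counts the before-minus-during difference among its measures of effect and does not say which analysis carries the impact claim.

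Third, other planned evidence bears on attribution: consent route is recorded, and uptake is to be related to intensity of implementation across schools. Both are useful, but neither settles which of the two tests decides.

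Fourth, model details are commonly left to an analysis plan. That holds for year effects and trend checks. It does not hold for the choice of contrast, because the article itself sets out both tests, their order and the basis for power.

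A reader might also infer that the baseline is 2014/2015 alone. The article does not say so: it covers five programme years, does not say how they are grouped into before and after, and does not date the two uptake figures.

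**Conclusion.** The point holds as a missing ranking of two planned tests. The uncontrolled test comes first, defines the risk difference and has the only power statement, and nothing reserves the impact claim for the controlled one. If the before/after result is read as an effect, a modest background rise is enough to mislead: about 21%, 64% or 94% for 1, 2 or 3 points. Those rises are assumptions. The article gives no trend, and a downward drift would hide an effect instead of creating one.

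Background trend carries the argument. It is tempting to infer from the low ranks that a sizeable rebound is bound to follow. Regression to the mean is possible, but the article gives nothing from which to put a figure on it.

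The 93% for the controlled contrast is an upper bound. It uses binomial variance only, and variation between authorities and years would lower it, with just two authorities on the intervention side. This is a cheap improvement to a design that already contains the right comparison.

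**What to change.** - Name the comparison of change against the comparison sites as the primary test of effect, and say that an impact claim rests on it.
- Analyse it as a difference-in-differences on annual uptake over the programme years already being collected, with local authority and year effects.
- Report the before/after difference in the intervention sites as descriptive.
- Add initial HPV uptake to the comparator criteria in the methods text, so that it agrees with the abstract.
- State power for the controlled contrast, with the size of the comparator and an allowance for variation between authorities.
- Check pre-intervention trends only as far as the number of pre-intervention years allows. The article gives no start date for the new procedures, and five annual points may leave few.

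The cost is small: the change is to wording and analysis, and both the site comparison and the five years are already planned. The price is a less precise estimate, with a standard error about 1.5 times that of the before/after difference for an equal-sized comparator and less than that for a larger one.

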### Process evaluation

The process evaluation will be conducted in line with the Medical Research Council guidance on process evaluation of complex interventions.^20^ An initial logic model will be developed, in consultation with health professionals, to show the hypothesised links between planned activities and inputs (self-consent procedures) and the sequence of short-term and medium-term outcomes (HPV vaccine implementation and uptake) that lead to desired longer-term outcomes (increased uptake, reduction in health inequalities). The initial logic model will be refined through experience and discussion as the study progresses, leading to an agreed logic model at the end of the study.

Context will be considered in relation to the socioecological model and will include examination of policy, organisational, interpersonal (family and peers) and intrapersonal factors. Questionnaires will be sent to a key contact in all secondary schools and relevant immunisation nurses in the two LAs. These will include questions about policies and procedures for HPV vaccination within schools. In addition, the researchers will compile fieldnotes when conducting observations and interviews in a sample of schools. Context will also be explored through interviews with a sample of immunisation nurses, school staff, young people and parents.

Similarly, the implementation and response to the new consent procedures will be examined through: questionnaires sent to a key contact in all secondary schools (including alternative educational settings) (n=58) and relevant immunisation nurses (n=5) in the two LAs; audio-recorded interviews (face to face or telephone) with relevant immunisation nurses, and more detailed qualitative research in eight schools (two mainstream and two alternative educational settings in each LA) purposively sampled in relation to type of school, HPV uptake, free school meal entitlement and percentage of students from minority ethnic groups. In these schools, more in-depth research will entail: audio-recorded focus groups or interviews (as preferred by participants) with approximately six young women; audio-recorded interviews with key school staff with responsibility for organising HPV vaccination sessions (one per school); observations of the process and setting for HPV vaccination and audio-recorded interviews or focus groups (as preferred by participants) with a purposive sample of approximately six parents per school.

Questionnaire responses will be reported descriptively, showing frequencies and percentages, and further illuminated by relevant free-text responses. All focus group and interview recordings will be transcribed verbatim and any potentially identifying information removed. Familiarisation with the data will involve two researchers reading and discussing the transcripts to compare and begin to code and categorise the data. Thematic analysis will be undertaken, assisted by the Framework approach to data management.^21^ Primary charts will be created using sections of the text relating to the context, views and experiences of self-consent. Streamlined versions of primary charts will be produced as the process of summarising and coding the data progresses. Key terms and phrases will be retained while repetition and extraneous text will be removed. Overarching themes will be identified within which similarities and differences will be explored.

